#### Adherence

Adherence will be determined as the proportion of prescribed IMST or aerobic exercise training sessions that were performed appropriately, i.e., correct duration and intensity. In the IMST group, adherence will be determined from the training session information saved on the internal data storage of the POWERBreathe K3 training device. In the aerobic exercise group, adherence will be assessed through heart rate data stored on the Polar OH1 heart rate monitor.

### Measurements related to lifestyle behaviors and body weight control

The following measures will be made at baseline and end-intervention to account for subject characteristics known to impact cardiovascular function. Physical activity will be monitored objectively via accelerometry (GENEActiv; 3-day recording) (Matthews et al., 2002) and subjectively via the Community Healthy Activities Model Program for Seniors questionnaire (Stewart et al., 2001) to ensure participant physical activity remains unchanged after versus before the intervention. Maximal oxygen consumption using indirect calorimetry during incremental treadmill exercise (Balke protocol) will be measured to document aerobic fitness (DeSouza et al., 2000). Body composition will be assessed by dual energy x-ray absorptiometry (DEXA) and anthropometry. Body mass also will be assessed during supervised training sessions and check-in visits (Visits 6-11, Figure 2).

### Selection of subjects and intervention administration

#### Study location and timeline

All study visits will be performed at the Clinical Translational Research Center (CTRC) at the University of Colorado Boulder Campus. We plan to recruit 90 subjects to account for an approximate 20% dropout rate to achieve our goal of completing testing on 72 participants.

#### Recruitment and eligibility

Recruitment efforts will include newspaper and social media advertisements; University of Colorado Boulder campus email bulletins sent to faculty, staff, and students; and flyers posted in public locations or handed out at senior centers and community fairs in the greater Boulder/Denver area. Interested individuals who contact the laboratory via telephone or email will be directed to fill out a general screening form (either over the phone or online) to determine their eligibility for the study. Interested individuals also can fill out the general screening form through a link provided on the laboratory website. Potential participants who meet the initial inclusion/exclusion criteria based on the general screening form will be contacted and scheduled for informed consent and screening visits. Individuals who do not meet inclusion/exclusion criteria also will be notified. Individuals will be allowed to ask any questions they have about the study at any point in the pre-consent process. All email, phone, and/or mail communication with potential participants will be kept confidential.

#### Informed consent and screening

Informed consent will be obtained in-person by a trained and approved member of the study team. The participant will be given an overview of the study and all study procedures, and have time to read through the informed consent document and invited to ask any questions. Both the participant and the investigator obtaining consent will sign the consent form and a copy of the signed form will be given to the participant. All study procedures have been reviewed and approved by the Institutional Review Board at the University of Colorado Boulder (Protocol #21-0489).

Following informed consent, participants will undergo screening assessments to further determine eligibility based on meeting enrollment criteria (Visits 1-2, Figure 2). Participants will be asked to abstain from food and caffeine for 5 h, alcohol and strenuous exercise for 24 h, and dietary supplements and non-prescription medications for 48 h before the screening visits. Screening assessments will include:• Resting BP and heart rate• Height and body weight• Medical history and physical examination• Exercise stress test• Ankle-brachial index• Questionnaire and paperwork• Family medical history• Physical activity *via* the Modifiable Activity Questionnaire (Kriska et al., 1990; Vuillemin et al., 2000)• Screening blood collection

Each participant’s results from screening will be reviewed by the study medical director, who will approve each individual’s safety for participating in the clinical trial.

#### Baseline assessments

Eligible participants who qualify for the study based on screening visits will undergo baseline experimental testing within a ≤10-day period (Visits 3-5, Figure 2). Participants will be asked to avoid major lifestyle changes for the duration of the study, including changes in physical activity, diet, and body weight, unless the changes are deemed necessary by the subject’s personal physician. Subjects will be asked to maintain a stable medication regimen through the study and to notify the study team should their physician recommend an immediate change to their medication prescriptions (change in medications or dosing).

#### Randomization and Blinding

After baseline assessments, participants will be randomized to 3 months of high-resistance IMST or aerobic exercise training. Block randomization will be employed based on age (≤64 years versus ≥65 years) and baseline SBP (elevated BP/stage 1 hypertension: 120–139 mmHg versus stage II hypertension: ≥140 mmHg) (Whelton et al., 2018). Randomization will be performed by a professional research assistant not involved with data analysis who will remain unblinded for the duration of the study. Investigators responsible for collection and analysis of outcome measures will be blinded to participant group assignment. Given the design of this study comparing different lifestyle interventions, participant blinding is not possible.

#### Intervention

##### High-resistance inspiratory muscle strength training

Participants in the high-resistance IMST group will train using the POWERBreathe K3 tapered-resistance inspiratory training device. Individual training sessions will entail performing 30 inspiratory maneuvers, consisting of 5 sets of 6 inspirations with a 1-min rest between sets. Training sessions will be performed 6 days per week for 3 months. Subjects will continue to train during the end-intervention testing period (described below) to maintain the training effect.

Inspiratory resistance on the POWERBreathe K3 will be set to 55% of each individual’s PI_MAX_ during week 1 of training, 65% of PI_MAX_ during weeks 2 and 3 of training, and then at 75% of PI_MAX_ throughout the remainder of the intervention. PI_MAX_ will be reassessed during supervised training sessions and check-in visits and the absolute training intensity adjusted to account for improvements in inspiratory muscle function throughout the intervention.

The first IMST training session will be supervised in the laboratory by an unblinded research assistant to train the participant on proper IMST technique (Visit 6, Figure 2). A second IMST training session will be supervised 1 week later to ensure maintenance of the proper technique (Visit 7, Figure 2). All other training sessions will be performed unsupervised, but with training documented by the internal storage of the POWERBreathe K3 training device.

PI_MAX_ will be assessed at baseline, during check-in visits (Visits 8-11, Figure 2) and during end-intervention testing to maintain an appropriate training stimulus and document changes in inspiratory muscle strength. To calculate PI_MAX_ subjects will perform a series of maximal inspiratory efforts against a near-infinite resistance using the POWERBreathe KH2 device and associated Breathlink software. The average of the 3 largest pressures generated will be calculated as PI_MAX_ (Kellerman et al., 2000; Vranish and Bailey, 2015). PI_MAX_ also will be measured at baseline and end-intervention in the moderate-intensity aerobic exercise group to allow for comparisons between groups.

##### Moderate-intensity aerobic exercise training

Subjects will walk at an intensity that elicits a heart rate between 40% and 60% of heart rate reserve, calculated as described previously (Tanaka et al., 1998). Resting heart rate will be measured during seated casual BP measurements and maximal heart rate will be determined from the maximal aerobic exercise test performed at baseline. Subjects will walk for 25 min per day, 6 days per week to meet aerobic exercise guidelines for 150 min/week of moderate-intensity exercise (Piercy et al., 2018) and to match the training frequency of the IMST group. During the aerobic exercise training sessions, a validated Polar OH1 heart rate monitor (Hettiarachchi et al., 2019) will provide real-time feedback to participants.

The first training session will take place on the laboratory treadmill, supervised by a research assistant, to familiarize the subjects with the appropriate exercise intensity and heart rate monitor use (Visit 6, Figure 2). A second aerobic exercise training session will be supervised 1 week later to confirm proper execution of training and to match subject contact time with the IMST group (Visit 7, Figure 2). All other sessions will be performed on-their-own, either outdoors or on a treadmill, with adherence documented by the heart rate monitor and recorded by a study investigator during check-in visits (Visits 8-11, Figure 2).

#### End-intervention assessments

After completing 3 months of either high-resistance IMST or aerobic exercise training, participants will return to the University of Colorado Boulder CTRC for reassessment of all outcome measures within a ≤10-day period (Visits 12-14, Figure 2). Participants will continue their assigned intervention throughout end-intervention testing to maintain the training stimulus. However, experimental testing will be scheduled to occur 24–48 h following the most recent training session to avoid any acute effects of the interventions. All end-intervention measurements will be identical to, and made under the same experimental conditions as, baseline testing.

#### Intervention abstention and follow-up testing

Once all end-intervention data have been collected, participants will return their training device (POWERBreathe K3 or Polar OH1 heart rate monitor) to the study staff and be instructed to halt their assigned intervention for a 6-week free-living period. During this 6-week period, participants will be asked not to make any lifestyle changes (outside of abstention from the study intervention). Participants will return to the laboratory 6 weeks later to perform follow-up testing for casual BP, 24-h BP, and FMD_BA_ (Visits 15 and 16, Figure 2) to determine the potential persistent effects of high-resistance IMST or moderate-intensity aerobic exercise on BP and vascular function (study primary and secondary outcomes).

#### Individual subject stopping criteria

Subjects will stop participation after successful completion of the study. Participants also can withdraw their informed consent at any time and for any reason. Investigators may also remove participants from the study at any time due to significant non-compliance with the protocol (i.e., procedures, assessments); any adverse event that, in the opinion of the medical director, indicates that continuing in the study is not in the best interest of the participant; loss of the participant’s ability to freely provide consent; or other serious changes in physical or mental health.

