• Subjects taking antihypertensive medications will be included provided they meet the other inclusion criteria, including SBP. Medication regimen (prescription and dosing) must be stable for at least 3 months prior to enrollment in the study and must remain stable during the study	

SBP, systolic blood pressure; DBP, diastolic blood pressure; ECG, electrocardiogram; METs, metabolic equivalents.

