#### Statistical design, power, and analysis plan

Sample size calculations and pre-determined statistical power for this randomized, single-blind, parallel group design clinical trial are based on the results from the estrogen-deficient postmenopausal women enrolled in our IMST pilot study (Craighead et al., 2021b) and results from a meta-analysis on the effects of aerobic exercise on SBP in our target population (Kelley, 1999).

Accordingly, it was estimated that aerobic exercise reduces casual SBP by 3.0 ± 3.7 mmHg (mean ± standard deviation), while high-resistance IMST reduces casual SBP by 7.6 ± 7.4 mmHg. With these parameters, it was estimated that 36 subjects per group (72 total) would provide 90% power to detect a difference in the change in casual SBP between groups with a two-sided type I error rate of *p* = 0.05. To account for a potential dropout rate of ∼20%, we will enroll 45 participants into each group (90 participants total).

Block randomization by age (midlife: ≤64 years; older ≥65 years) and baseline SBP (elevated SBP/stage 1 hypertension: 120–139 mmHg; stage 2 hypertension: ≥140 mmHg) will be employed. Data for all outcome variables will be collected at baseline and at the end of the respective 3-month interventions. In addition, casual BP, 24-h BP and FMD_BA_ will be collected after abstaining from the interventions for 6 weeks to assess potential persistent effects of previous training on these outcomes.

Descriptive statistics will be calculated for all baseline and outcome variables. Means and standard deviations will be calculated for all continuous variables, and frequency and proportion will be provided for all categorical variables. Data transformation will be performed if appropriate. The 95% confidence interval will be calculated as needed.

Repeated measures analysis by linear mixed effects models will be used to assess changes in casual and 24-h BP and FMD_BA_. Data from baseline, end-intervention and 6 weeks after completing the intervention will be included in the model. Based on this model, comparisons in the changes in BP between the two groups will be performed to assess the treatment effect. The basic model will include group, measurement timepoint, and the group by time interaction. Potential confounders such as time post menopause or use of antihypertensive medications can be included for adjustment purposes.

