**FIGURE 3 F3:**
[figure not shown]
Expected Results. Expected results for **(A)** casual systolic blood pressure (SBP; primary outcome) and 24-h SBP (secondary outcome); and for **(B)** endothelial function measured by brachial artery flow-mediated dilation (FMD_BA_; secondary outcome) in the high-resistance inspiratory muscle strength training (IMST) and moderate-intensity aerobic exercise groups across the intervention. Dashed line represents expected FMD_BA_ with supratherapeutic infusion of the potent antioxidant, vitamin C, in both subject groups.

We also expect a greater improvement in FMD_BA_ following high-resistance IMST compared to aerobic exercise training, and that the improvement in FMD_BA_ following IMST will be at least partially sustained 6 weeks later (Figure 3B).

At end-intervention, we anticipate that high-resistance IMST will reduce or abolish the acute increase in FMD_BA_ observed after systemic infusion of vitamin C at baseline, but that aerobic exercise training will have no effect (Figure 3B). We expect that in biopsied endothelial cells, high-resistance IMST will decrease nitrotyrosine (marker of oxidative stress), decrease the expression of the oxidant enzyme NADPH oxidase, and increase expression of the antioxidant enzyme MnSOD to a greater extent than aerobic exercise training. We also expect endothelial cells cultured with subject serum obtained after (vs. before) IMST will increase NO and decrease ROS production more than serum obtained after (vs. before) aerobic exercise training. We also expect to identify changes in circulating metabolites with IMST that more greatly modulate endothelial cell NO and ROS production than aerobic exercise training does.

In addition, we expect to observe higher rates of adherence to the high-resistance IMST intervention compared to aerobic exercise training. Finally, we expect to observe fewer intervention-related adverse events and dropouts due to adverse events in the IMST group, suggesting greater safety and tolerability of IMST compared to aerobic exercise.

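### The stopping criteria let investigators remove women from the study, not only from training, for non-compliance; this ends outcome collection and can bias the primary comparison in either direction

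*Protocol article*

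**What the plan says.** Under Individual subject stopping criteria: "Investigators may also remove participants from the study at any time due to significant non-compliance with the protocol (i.e., procedures, assessments". The same section lists other grounds: withdrawal of consent, adverse events as judged by the medical director, loss of the ability to consent, and serious changes in health.

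Training adherence is handled separately, as an outcome: "Adherence will be determined as the proportion of prescribed IMST or aerobic exercise training sessions that were performed appropriately" (Adherence). It is compared between groups by an unpaired t-test (Statistical design, power, and analysis plan). Under Expected results and their interpretation, "we expect to observe higher rates of adherence to the high-resistance IMST intervention compared to aerobic exercise training". In the aerobic arm, adherence is "recorded by a study investigator during check-in visits" (Moderate-intensity aerobic exercise training).

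The primary analysis is a linear mixed model with group, time and their interaction, using data from baseline, end-intervention and 6 weeks after the intervention. The planning values are that "aerobic exercise reduces casual SBP by 3.0 ± 3.7 mmHg" and "high-resistance IMST reduces casual SBP by 7.6 ± 7.4 mmHg". The target is 36 completers per group, with 45 per group enrolled to allow for about 20% dropout.

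On medication, Table 1 says the antihypertensive regimen "must be stable for at least 3 months prior to enrollment in the study and must remain stable during the study". Baseline assessments asks for a stable regimen and for the team to be told if a physician recommends an immediate change.

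**The concern.** Stopping the assigned training and leaving the study are different events, and the rule does not separate them. Removal happens after randomisation, at the investigators' discretion and without a stated threshold. If poor training adherence counts as non-compliance, the women whose outcomes are lost are those who trained least, and the sponsor expects that group to differ in size between arms.

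The article presents the trial as a comparison of effectiveness and names poor adherence as a weakness of aerobic exercise. A contrast that drops non-adherers would answer a narrower question, and randomisation would no longer fully protect it. Adherence is also an outcome, so removing the least compliant women can distort that comparison too. An analysis plan can define a population, but it cannot recover a 3-month blood pressure that was never measured.

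**Working it through.** **1. The plan's own figure.** Inputs from Statistical design, power, and analysis plan: mean reductions 7.6 and 3.0 mmHg, SDs 7.4 and 3.7, two-sided alpha 0.05, power 90%.

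- Planned difference: 7.6 - 3.0 = 4.6 mmHg.
- Average SD: sqrt((3.7² + 7.4²)/2) = sqrt(34.225) = 5.85.
- Required per group: 34 (normal approximation), 35 (pooled t-test), 36 (Welch t-test). Power at 36 per group with Welch is 90.5%.
- Enrolment: 36/(1 - 0.20) = 45 per group, 90 in total.

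The stated sample size reproduces. The point does not rest on a sample-size error.

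**2. What the model sees.** A woman removed during training contributes only her baseline value. The blood pressures taken at training and check-in visits are not among the data listed for the model, and adherence is not in the basic model. Her missing change is therefore implicitly predicted from women retained in the same arm. That is safe only if the missingness is explained by the data in the model.

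**3. Size under assumptions.** The documents give neither removal rates nor the response of removed women. Assume:

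- women who are retained respond at the planning means;
- a share q_I of the IMST arm and q_A of the aerobic arm is removed before end-intervention testing;
- removed women keep a fraction f of their arm's effect (0 or 0.5);
- baseline pressure does not predict who is removed.

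The difference among all randomised women is 7.6 × [1 - q_I(1 - f)] - 3.0 × [1 - q_A(1 - f)]. The difference among retained women is 4.6. Retained minus all-randomised gives

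bias = (1 - f) × (7.6 q_I - 3.0 q_A).

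Examples with f = 0: at 0% and 20% removed, 0 - 0.60 = -0.60; at 20% and 20%, 1.52 - 0.60 = +0.92.

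| Removed, IMST / aerobic | Bias, f = 0 (mmHg) | Bias, f = 0.5 (mmHg) |
|---|---|---|
| 0% / 20% | -0.6 | -0.3 |
| 5% / 30% | -0.5 | -0.3 |
| 5% / 20% | -0.2 | -0.1 |
| 10% / 20% | +0.2 | +0.1 |
| 5% / 5% | +0.2 | +0.1 |
| 20% / 20% | +0.9 | +0.5 |

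A negative value understates the IMST advantage and a positive value overstates it. The sign changes where q_I/q_A = 3.0/7.6 = 0.39. Even equal removal in both arms gives a positive bias, because the assumed IMST effect is larger.

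**4. Scale.** The extremes are 0.60/4.6 = 13% and 0.92/4.6 = 20% of the planned difference. The standard error of that difference with 36 per group is sqrt((3.7² + 7.4²)/36) = 1.38 mmHg, so the extremes are about 0.4 and 0.7 of a standard error.

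**5. Sensitivity to convention.** If the planning means are instead taken to describe all randomised women, 0%/20% with f = 0 gives a retained aerobic mean of 3.0/0.8 = 3.75 and a bias of -0.75. At 20%/20% it is 7.6/0.8 - 3.75 - 4.6 = +1.15. The range in the table is therefore an illustration, not a bound.

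**The case against.** The strongest objection is that the rule itself spells out non-compliance as procedures and assessments. Training is not named, the article treats training adherence as a separate outcome, and it states no adherence threshold for removal. This stands as a limit on the point. A reader might infer that the sponsor predicts more removals in the aerobic arm. The documents predict only lower training adherence there, and the link to removal is a possible reading. Under the narrow reading, a woman who refuses all assessments has missing outcomes with or without the rule. But a woman who misses some assessments could be removed rather than invited to the next ones.

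A reader might also infer that outcome data are deleted. They are not: nothing says that collected data are discarded, the mixed model can use them, and a woman removed after Visit 14 already has her 3-month result. What is lost is later collection.

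Nor do the documents show that the comparison will be biased, or biased towards IMST. The rule is permissive, no rate is given, and removal mainly of aerobic participants would shrink the IMST advantage. The larger scenarios are also demanding: 20% of 45 is 9 women, the whole dropout allowance of an arm (45 - 36 = 9).

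On blinding, "Investigators responsible for collection and analysis of outcome measures will be blinded to participant group assignment". The article does not say who decides on removal for non-compliance, so it cannot be said that these decisions are made with knowledge of the arm, or that they are shielded from it.

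The medication wording might be read as a second exclusion after randomisation. The stopping criteria do not list a medication change, so that is not supported. Finally, the lack of a named analysis population is not a fault in a condensed article. The point rests on a rule that is stated.

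**Conclusion.** The point holds as a risk created by a stated rule. Investigators may end study participation for non-compliance, without a threshold, and so stop outcome collection in women who may differ in response and in number between arms. The primary comparison can be biased in either direction, by about -0.6 to +0.9 mmHg against 4.6 mmHg. That range assumes removal of 0-20% (IMST) and 5-30% (aerobic) and that removed women keep none or half of the effect. The strongest mechanism, removal for poor training adherence, also requires the broader reading of procedures. The effect is modest relative to the standard error, but its sign cannot be known in advance and the analysis cannot correct it once the visits are missed. The distortion of the adherence comparison is possible but cannot be sized from the documents. The change is worth making because it is cheap. The medication wording is a smaller matter of consistency.

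**What to change.** Remove non-compliance as a ground for leaving the study. State that women who do not follow or who stop the assigned training, and who still consent, are invited to the remaining outcome visits (Visits 12-16) and are analysed in the arm to which they were randomised. Any compliers-only analysis should be labelled supportive. Leave the section's other grounds as they are: withdrawal of consent, adverse events as judged by the medical director, loss of the ability to consent, and serious changes in health. This concerns only whether outcomes continue to be collected, not any clinical decision about training.

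Separately, reconcile the Table 1 wording on medication stability with Baseline assessments, so that it is clear what a physician-recommended change means for participation.

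The cost is a change of protocol wording and some extra effort to bring non-adherent participants back to visits that the schedule already contains.
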